### Blood and urine collection

3.1

Visit 1 is scheduled in the morning and participants are instructed to eat only a light, nonfat containing breakfast. Medication known to interfere with laboratory tests is discontinued for at least 10 days prior to testing. During visit 1 a maximum of 100 mL of blood and 10 mL of urine is collected from each participant. These samples are either stored or immediately processed for advanced hemostasis testing, platelet function tests, targeted proteomics, assessment of vascular markers, and, if consent has been provided, DNA gene panel testing for undiagnosed bleeding and platelet disorders. Not all investigations are performed in all participants because some tests require fresh whole blood and can only be performed in centers where this test is available (eg, ATP release and Maastricht flow chamber). If a test has already been performed in the participating center before BDUC diagnosis, the test is not repeated. Performed tests are shown in Table 2. After 5 and 10 years of follow-up, an additional blood sample (30 mL) is collected for VWF activity and antigen, FVIII, thrombin generation, and plasma proteomics among others.

**Table 2 tbl2:** Performed blood tests at baseline and follow-up visits^a^.

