The objective is to assess the diagnostic yield of advanced hemostasis and fibrinolytic tests and targeted proteomics of TIER1 hemostatic proteins in BDUC and evaluate these over time. In WP5, we will perform advanced hemostasis and fibrinolytic tests eg, assessment of rare factors deficiencies, modified thrombin generation assays and tissue plasminogen–activated rotational thromboelastometry, to assess their diagnostic yield in BDUC. Previous studies demonstrated hyperfibrinolytic profiles in a subset of persons with BDUC, supporting further evaluation of fibrinolytic pathways using tissue plasminogen–activated rotational thromboelastometry [20]. Moreover, targeted proteomics will be performed according to the ISTH-Tier1 gene list [28,29]. These assays aim to elucidate abnormalities in coagulation and fibrinolytic pathways. To assess intraindividual changes over time, blood samples will be collected at 5 and 10 years after study inclusion for longitudinal evaluation of hemostatic parameters. Particular attention will be given to the well-known age-related increase in von Willebrand factor (VWF) levels [30], and its impact on diagnostic reclassification and bleeding phenotype.

#### Workpackage 6

2.1.6

The objective is to assess the diagnostic yield of advanced (flow dependent) platelet function tests in BDUC. In WP6, we will assess the diagnostic yield of advanced (flow-dependent) platelet function tests (eg, the Maastricht flow chamber [12], β-thromboglobulin, and platelet serotonin content). A subset of participants with a possible platelet function disorder will be reinvited for an additional blood withdrawal to perform platelet proteomics at Sanquin Research to investigate for qualitative and/or quantitative defects in the platelet proteome [31,32].

#### Workpackage 7

2.1.7

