**Inclusion criteria**	
Age ≥12 y	
Referred to a (pediatric) hemostasis specialist for evaluation of bleeding tendency	
Increased bleeding tendency based on: - Abnormal ISTH-BAT score (≥5 in women aged 18-30 y, ≥6 in women aged 31-51 y, and ≥7 in women age 52 y or older; ≥4 in men; and ≥ 3 in children) [41] OR - Clinical gestalt according to the investigating physician	
Absence of diagnostic test results for a bleeding disorder in standard laboratory hemostasis tests:	
Laboratory test	For inclusion should be
Complete blood count	Hemoglobin > 6.0 mmol/L; thrombocyte count > 100 × 10^9^/L
PT, aPTT	Within local reference range, or prolonged without explanatory factor deficiency
Fibrinogen activity; VWF antigen and activity; and FVIII, FIX, FXI, and FXIII	Within local reference range or abnormal but not explaining bleeding phenotype
Light transmission aggregometry	Not diagnostic for a platelet function disorder or not explaining bleeding phenotype
Kidney function: EGFR	> 45 mL/min
Liver function: ALAT, bilirubin	< 3× ULN

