**Exclusion criteria**	
Use of medication interfering with laboratory hemostasis tests, which cannot be stopped before blood withdrawal (eg, anticoagulant or antiplatelet therapy and NSAIDs)	
Pregnancy or lactation at moment of inclusion	
Presence of a known bleeding disorder	
Presence of an acquired cause or another explanation for the increased bleeding tendency	
Inability to provide informed consent	

ALAT, alanine aminotransferase; aPTT, activated partial thromboplastin time; EGFR, estimated glomerular filtration rate; F, factor; ISTH-BAT, International Society on Thrombosis and Haemostasis—Bleeding Assessment Tool; NSAID, nonsteroidal anti-inflammatory drug; PT, prothrombin time; VWF, von Willebrand factor.

A potential participant will be excluded in case of use of medication interfering with laboratory hemostasis tests, which cannot be stopped before blood withdrawal; pregnancy or lactation at moment of inclusion; presence of an established bleeding disorder [[42], [43], [44]]; presence of an acquired cause or another explanation for the increased bleeding tendency; or inability to provide informed consent.

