**Figure 2 fig2:**
[figure not shown]
Overview of study procedures. BDUC, bleeding disorder of unknown cause; EPR, electronic patient record; ISTH-BAT, International Society on Thrombosis and Haemostasis—Bleeding Assessment Tool; WES, whole exome sequencing.

During visit 1, blood samples and a urine sample are collected. After this visit, information is obtained from the electronic patient record (EPR) by the research team, and questionnaires are sent digitally or on paper to participants to be completed at home. After ∼2 months, a telephone consultation is scheduled (visit 2). During this visit, the ISTH-BAT and hypermobility are scored by a trained and experienced researcher. Moreover, missing information from the EPR and online questionnaires are completed. Follow-up consists of an annual telephone consultation and check of the EPR by the study team to collect data on bleeding symptoms, ISTH-BAT score, hemostatic challenges, treatment, and outcomes. At 5 and 10 years after inclusion, another visit to the treatment center is scheduled (visit 3 and visit 4, respectively) to collect an additional blood sample, and digital questionnaires are repeated. Treatment center visits and blood collection are coordinated with routine clinical visits or scheduled venipunctures if possible to minimize participant burden.

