**(Advanced) tests for platelet function disorders at baseline**	
Global platelet function tests	Complete blood count in PLT-F modus with immature platelet fraction
Platelet nucleotide assessment	ATP-release, ATP/ADP, platelet serotonin content, and β-TG
Flow-based platelet function tests	Maastricht flow chamber^b^, T-TAS^b^, Anysis^b^, and PFA-200
Flowcytometry	VWF, GP1b, CD49b, CD41a, and GPVI
Platelet activation test (PACT)	PAR1, PAR4, ADP, CRP, and U46619 for fibrinogen/p-selectin expression
**Longitudinal****follow-up****at 5 and 10 y**^c^	
Hemophilia/VWD	FVIII and VWF antigen and activity
Global hemostasis (dys)function	Thrombin generation^b^
Proteomics	Plasma proteomics^b^

ALAT, alanine aminotransferase; AP, antiplasmin test; ECLT, euglobulin clot lysis time; EGFR, estimated glomerular filtration rate; NATEM, nonactivated rotational thromboelastometry; PAI, plasminogen activator inhibitor; PFA, platelet function analyzer; PLT-F, fluorescence platelet count; ROTEM, rotation thromboelastometry; tPA, tissue-type plasminogen activator; TAFI, thrombin-activatable fibrinolysis inhibitor; TFPI, tissue factor pathway inhibitor; TG, thromboglobulin; TSH, thyroid-stimulating hormone; T-TAS, total thrombus formation analysis system; VWD, von Willebrand disease; VWF, von Willebrand factor.

a If a test has already been performed in the participating center, the test is not repeated.

b Research-based tests.

c Based on preliminary results and new insights, additional assessments may be added to follow-up evaluations.

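### The no-repeat rule lets VWF and FVIII go unmeasured at visit 1 in participants worked up in their own center, so their 5- and 10-year change lacks a standardised, time-aligned baseline

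*Protocol article*

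**What the plan says.** Four parts of the protocol article bear on this.

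- **Eligibility.** Table 1 lists "Fibrinogen activity; VWF antigen and activity; and FVIII, FIX, FXI, and FXIII" among the standard tests needed for inclusion. They are judged against the local reference range, and abnormal values are accepted if they do not explain the bleeding. Section 3 has the criteria met before consent is signed at the start of visit 1, so these results predate visit 1.
- **The rule.** Section 3.1 states "If a test has already been performed in the participating center before BDUC diagnosis, the test is not repeated". Table 2 footnote a states "If a test has already been performed in the participating center, the test is not repeated", without the limit to the period before diagnosis. Neither exempts any test.
- **Baseline and follow-up tests.** Table 2 lists VWF activity and antigen and FVIII (one-stage and chromogenic) at baseline, and "FVIII and VWF antigen and activity" again at 5 and 10 years.
- **Purpose.** Workpackage 5 (section 2.1.5) takes the later samples to assess within-person change, at times counted from study inclusion. It adds: "Particular attention will be given to the well-known age-related increase in von Willebrand factor (VWF) levels", together with its effect on diagnostic reclassification and bleeding phenotype.

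**The concern.** A within-person change needs a first measurement comparable with the later ones and taken at the time the clock starts. Followed as written, the rule can remove that measurement for the very parameter that Workpackage 5 singles out, because every participant must already have it to be eligible.

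The substitute is a clinical result from the patient record. It may be older than inclusion by an unknown amount, it was produced by the local method of its day, and it was not necessarily drawn under visit-1 conditions. Part of any apparent rise would then belong to the time before inclusion. A participant whose VWF had already risen before visit 1 could be counted as changing, or as reclassified, during follow-up. The lag would also differ systematically between existing-cohort members and newly diagnosed patients.

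**Working it through.** **1. The plan's own figure.** The only precision stated (section 3.5) is ±3.5% for a 20% diagnostic yield in 500 participants. Half-width = 1.96 × √(0.20 × 0.80 / 500) = 0.0351, or 3.5 percentage points. It reproduces, and this point does not affect it. The plan gives no figure for the VWF or FVIII change.

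**2. Reading the sections together.**
- Table 1 and section 3: VWF antigen, VWF activity and FVIII are known before visit 1.
- Section 3.1 and footnote a: if they were done in the participating center, they are not repeated.
- Table 2 and section 2.1.5: they are measured again at 5 and 10 years after inclusion, for within-person change.

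For a participant worked up in their own center, the first value is therefore the diagnostic one. If the work-up was done elsewhere, the rule does not apply and visit 1 supplies the value.

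**3. How many could have an old value.** Section 3.5 says about 300 people in three existing cohorts will be invited. As a share of 500, with assumed joining rates:
- all join: 300/500 = 60%
- 80% join: 240/500 = 48%
- 60% join: 180/500 = 36%

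These are upper limits for that group, since some may have been tested outside their participating center.

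**4. Interval actually covered.** The lag L between the diagnostic result and inclusion is not given, so L is an assumption. The nominal 5-year change spans 5 + L years and the nominal 10-year change 10 + L.

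| Assumed L (years) | Span of 5-year change | (5 + L)/5 | (10 + L)/10 |
|---|---|---|---|
| 0.5 | 5.5 | 1.1 | 1.05 |
| 1 | 6 | 1.2 | 1.1 |
| 2 | 7 | 1.4 | 1.2 |
| 5 | 10 | 2.0 | 1.5 |
| 10 | 15 | 3.0 | 2.0 |

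For a mixed cohort, assume 60% with L = 5 and 40% with L = 0.5. The mean lag is 0.6 × 5 + 0.4 × 0.5 = 3.2 years, so the 5-year change covers 8.2 years on average: 10 in one group and 5.5 in the other.

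**5. What dating the old value would not repair.**
- *Assay.* Assume a within-person SD of 15% on the log scale. The variance of a change is 2 × 0.15² = 0.045. An assumed 10% SD for a change of method between the two values adds 0.10² = 0.010, and 0.010/0.045 = 22%.
- *Selection on the eligibility value.* A simulation assumed a true rise of 0.7% a year, between-person SD 30%, within-person SD 15%, mean VWF 90 to 110 IU/dL, entry only above 50 IU/dL and no lag. It gives an apparent rise of 0.58 to 0.67% a year. This effect is minor, and Table 1 applies no hard cut at 50.

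**The case against.** The strongest reply is that a reader could infer much more than the text supports.

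- *That VWF and FVIII will not be measured at visit 1 in anyone, leaving no baseline.* The rule covers only tests done in the participating center. Assays not yet done there, such as chromogenic FVIII, would still be run. Section 3.2 collects the laboratory results from the time of diagnosis, so an earlier value exists and can be dated. Visit-1 samples may be stored, although no VWF or FVIII assay on them is promised. The comparison of year 5 with year 10 uses two study samples.
- *That all the longitudinal tests are affected.* Thrombin generation and proteomics are research-based and not needed for inclusion, so they will generally have a visit-1 value.
- *That the yearly rise will be overstated by the ratios in the table.* That requires dividing a longer change by 5 or 10. The protocol states no such analysis, and how elapsed time is modelled is commonly left to an analysis plan.
- *That follow-up samples are drawn under looser conditions.* The sentence "Treatment center visits and blood collection are coordinated with routine clinical visits or scheduled venipunctures if possible to minimize participant burden" covers center visits in general, not visits 3 and 4 alone. "Pregnancy or lactation at moment of inclusion" is an entry criterion; handling pregnancy at later draws is detail that an article commonly leaves to the full protocol.
- *That fibrinolysis tests are promised over time but dropped.* The Workpackage 5 objective does cover them along with "targeted proteomics of TIER1 hemostatic proteins in BDUC and evaluate these over time", and the follow-up list names none. But section 3.1 leaves that list open, and Table 2 footnote c allows additions.

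These replies narrow the point without removing it. Modelling elapsed time corrects the lag, but not differences in assay, sampling conditions or selection on the eligibility value. It is also fair that longitudinal VWF is one aim within one of eleven workpackages.

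**Conclusion.** The concern holds in a limited form. Where the work-up was done in the participant's own center, the rule as written allows the baseline VWF antigen, VWF activity and FVIII to be an earlier local result of unspecified date and method. The 5- and 10-year change timed from inclusion then lacks a standardised, time-aligned starting point.

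The size depends on a lag that the documents do not give. The nominal 5-year change would cover 5.5 years at a lag of six months and 10 years at a lag of five years. It is a small matter for newly diagnosed participants and may be a substantial one for existing-cohort members. The documents do not support saying that no baseline exists or that a particular overstatement of the VWF rise will follow. The point merits action before enrolment because a value neither assayed nor banked at visit 1 cannot be recovered at year 5.

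**What to change.** 1. In section 3.1 and Table 2 footnote a, exempt VWF antigen, VWF activity and FVIII from the no-repeat rule, or commit to assaying them in stored visit-1 plasma, in all participants.
2. Where only a historical value exists, record its date and assay, and model change over the time actually elapsed.
3. Align the two statements of the rule. Only section 3.1 limits it to tests done before the diagnosis. Footnote a hangs on a table that also covers follow-up, so read literally it would cancel the 5- and 10-year tests as well; limit it to baseline tests.

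The cost is a few routine assays on at most 500 samples and a short change of wording. Section 3.1 already provides for up to 100 mL of blood at visit 1, so no extra visit or venipuncture is needed.

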**(Advanced) hemostasis tests at baseline**	
Rare coagulation factor deficiency	FII, FV, FVII, and FX
Hemophilia/VWD	VWF activity and antigen, VWF collagen binding, 1-stage and chromogenic FVIII, and ABO blood group
Fibrinolysis disorders	Fibrinogen, PAI-1 activity and antigen, tPA, plasminogen, TAFI, α2-AP, lysis timer test, ECLT, plasmin generation test, and tPA-ROTEM
Anticoagulant abundance	D-dimer, antitrombin, protein C, protein S, and TFPI
Global hemostasis (dys)function	Thrombin generation^b^ and NATEM-ROTEM
Other causes for bleeding	TSH, ALAT, creatinine, EGFR, and vitamin C
Proteomics and genetic testing (if consent is present)	Targeted and unbiased proteomics^b^ and WES panel hemostasis and thrombosis (TIER-1 genes)
**(Advanced) tests for platelet function disorders at baseline**	
Global platelet function tests	Complete blood count in PLT-F modus with immature platelet fraction
Platelet nucleotide assessment	ATP-release, ATP/ADP, platelet serotonin content, and β-TG
Flow-based platelet function tests	Maastricht flow chamber^b^, T-TAS^b^, Anysis^b^, and PFA-200
Flowcytometry	VWF, GP1b, CD49b, CD41a, and GPVI
Platelet activation test (PACT)	PAR1, PAR4, ADP, CRP, and U46619 for fibrinogen/p-selectin expression
**Longitudinal****follow-up****at 5 and 10 y**^c^	
Hemophilia/VWD	FVIII and VWF antigen and activity
Global hemostasis (dys)function	Thrombin generation^b^
Proteomics	Plasma proteomics^b^

ALAT, alanine aminotransferase; AP, antiplasmin test; ECLT, euglobulin clot lysis time; EGFR, estimated glomerular filtration rate; NATEM, nonactivated rotational thromboelastometry; PAI, plasminogen activator inhibitor; PFA, platelet function analyzer; PLT-F, fluorescence platelet count; ROTEM, rotation thromboelastometry; tPA, tissue-type plasminogen activator; TAFI, thrombin-activatable fibrinolysis inhibitor; TFPI, tissue factor pathway inhibitor; TG, thromboglobulin; TSH, thyroid-stimulating hormone; T-TAS, total thrombus formation analysis system; VWD, von Willebrand disease; VWF, von Willebrand factor.

a If a test has already been performed in the participating center, the test is not repeated.

b Research-based tests.

c Based on preliminary results and new insights, additional assessments may be added to follow-up evaluations.

### Data collection from EPRs

3.2

EPRs are reviewed to collect data on demographic and socioeconomic characteristics, as well as clinical data such as reasons for initial referral, bleeding symptoms, a medical history, a family history, medication use, contraceptive use, and the diagnostic pathway leading to BDUC diagnosis, including BAT score and performed laboratory tests at time of BDUC diagnosis. Additionally, details regarding treatment plans and outcomes related to invasive procedures, bleeding episodes, and childbirth within the past 5 years are collected. This includes type of intervention and associated outcomes (eg, bleeding, re-surgery, prolonged hospital stays, and use of hemostatic agents and blood products). These data are also documented throughout the follow-up period by annual review of the EPR.

### Online questionnaires

3.3

Standardized questionnaires are administered to collect data on sociodemographic details, physical activity, mental health, social participation, and, in women and girls, HMB-specific QoL. Adult participants will complete the short form (SF)/RAND-36 questionnaire, the generic patient-reported outcome measure (PROM) questionnaire, and the short questionnaire to assess health-enhancing physical activity (SQUASH) and, for women, additionally, the menorrhagia multiattribute scale (MMAS). Children will complete the pediatric quality of life inventory (PEDsQL), PROM pediatric measures, and SQUASH, and, for girls, additionally, the MMAS.

### Additional study procedures

3.4

A selection of study participants, if consent to be reinvited is present, will be invited for additional study procedures (Figure 2), based on specific clinical or laboratory characteristics and results from WPs. These additional procedures include an additional blood withdrawal to perform advanced hemostasis tests (WP5 and WP6), flow chamber experiments (WP10), multiomics analysis (WP8), and endothelial cell models (WP9); participation in semistructured interviews or focus groups to explore patient experiences and needs regarding BDUC (WP3); completion of additional online questionnaires (WP2); and for adults (age ≥ 18, including those who reach adulthood during the course of the study), genetic counseling and additional informed consent for open exome analysis and WGS (WP8).

### Sample size

3.5

The BDUC-iN study consists of multiple workpackages with distinct objectives and end points. Therefore, no single conventional power calculation based on 1 primary outcome was considered appropriate. The planned sample size was primarily based on feasibility and the expected precision of estimating the diagnostic yield of advanced hemostatic testing in BDUC. Previous studies and preliminary data suggest that extended laboratory investigations may identify clinically relevant abnormalities in ∼20% of individuals currently classified as having BDUC [20,45]. Assuming a diagnostic yield of 20%, inclusion of 500 participants allows estimation of this proportion with a 95% confidence interval of approximately ±3.5%. Furthermore, this sample size is expected to yield ∼100 participants with an abnormal laboratory phenotype, facilitating exploratory subgroup analyses across the different workpackages. Given the rarity and heterogeneity of BDUC, inclusion of 500 participants is considered both feasible and scientifically meaningful. Within 3 existing Dutch cohort studies, ∼300 individuals with BDUC are currently registered, who will be invited for inclusion in the BDUC-iN study. Willingness to participate was high in prior studies. As the incidence of BDUC in the Netherlands is estimated at ∼50 to 100 new cases per year, a total enrolment of ∼500 participants over the entire study period is considered realistic.

### Ethics and dissemination

3.6

The BDUC-iN study protocol was approved by the Medical Ethical Research Committee of the Maastricht University Medical Center, Maastricht, Netherlands (NL87370.068.24), and registered at ClinicalTrials.gov (NCT07454161) and the Overview of Medical Research in the Netherlands (NL-OMON57561). Approval by the local Medical Ethical Research Committees of participating treatment centers is currently under review. All amendments to the protocol will be submitted to the Medical Ethical Research Committee and to the competent authority.

Study procedures are conducted in accordance with the principles of the Declaration of Helsinki and the Medical Research Involving Human Subjects Act (WMO). Informed consent is obtained from all participants for study participation with use of data for research purposes. In case of open and WGS, there is a risk of incidental findings. Participants and their treating physicians are informed about unsolicited findings that require follow-up care or in case of relevance for their offspring.

Participant enrollment will start on March 1, 2026, with an inclusion period of up to 5 years. All study participants will subsequently be followed up for a 10-year period. Results from the different participating treatment centers will be analyzed in close collaboration with these centers and submitted for publication in international peer-reviewed journals as well as presented at scientific conferences. Depending on the research question, 1 or more participating centers will take the lead in the analysis of results and preparation of the manuscripts for publication, after approval by the principal investigator and the BDUC-iN steering committee.

